### Patient and public involvement

Involvement of the public and stakeholders in the early stages of this study confirmed that the potential impact of exercise on blood glucose control, especially hypoglycaemia, is a common concern for people living with diabetes. Study design was enhanced by capturing the views of several patients with insulin treated diabetes. They reflected on the relevance and importance of the study, study documentation and approach, and potential dissemination strategies for the public. Two PPI members are actively involved in this trial, influencing design and conduct. Their input will be supported according to National Institute for Health Research (NIHR) Centre for Engagement and Dissemination guidance.

### Study outcomes

#### Feasibility outcomes

The primary aim of this study is acceptability and feasibility of procedures for recruitment and retention, randomisation and adherence and fidelity to the resistance training programme intervention. We will use a traffic light approach, where green=proceed without modification; amber=proceed but with modification, red=unrealistic to proceed without major modification. Recruitment rates will be calculated as the rate of invited participants who are eligible, who subsequently provide informed consent. Green ≥50% recruitment, amber=25%–50% recruitment, red ≤25% recruitment. Attrition rates will be measured, defined by discontinuation of the resistance training intervention and/or lost to follow-up measurement for both conditions. Green ≤10% attrition, amber=10%–20% attrition, red ≥20% attrition. Reasons for attrition will be explored qualitatively. Acceptance, adherence and fidelity to the resistance training intervention will be monitored by the research team, who will measure session attendance: green ≥90% attendance, amber=75%–90% attendance, red ≤75% attendance, plus participant following intervention instructions >75% of the time, and participant self-report. Preintervention and postintervention qualitative interviews will be used to assess the acceptability of the resistance training intervention, influences on diabetes self-management where applicable, and well-being more generally, at baseline and at 5 weeks. Information about adverse events will be collected for the intervention group.

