## Methods and analysis

### Study design

This is a single-centre interventional feasibility randomised controlled trial with an associated baseline case–control descriptive observational component, and a qualitative and process evaluation component, conducted in Newcastle upon Tyne, England. Thirty participants with insulin treated diabetes and mild frailty, and thirty without diabetes will be recruited. All participants will be aged ≥60. All participants will undergo blood and physical testing, for the baseline case–control component. The diabetic participants will then go forward into the trial. They will be randomised 1:1 to the intervention group, which is a 4-week programme of supervised resistance exercise training, or to the control group; to carry on with any usual activity as normal. The current version of the protocol is V.3.

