### Identification, recruitment and consent procedures

All potential participants will be identified through the following methods: by their treating clinician who is a clinical member of the research team, in clinic at the Newcastle Diabetes Centre (applicable to those with diabetes only); via poster adverts in general practitioner (GP) practices and other secondary care clinics; GP practice database searches facilitated by the North East and North Cumbria Clinical Research Network; via social media; and via the Newcastle United Foundation charity. All methods have been reviewed and approved by the Health Research Authority and the study sponsor, through their ethical and governance review processes.

A participant information sheet will be sent to potential participants. Informed written consent will be given and eligibility confirmed by a member of the research team. Potential participants will then be screened with the Rockwood Clinical Frailty Score, by either their treating diabetes clinician (where applicable) or by a member of the research team. The study will take place from December 2020 to September 2022.

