### Randomisation

After completing the initial testing procedures, the diabetic group (n=30) will be randomised in a 1:1 ratio to either the intervention group (4-week supervised resistance training programme), or the control group (see figure 1).

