### Intervention

The intervention is a 4-week, semistructured resistance exercise training programme, designed to increase muscle mass and strength. Training will be carried out at participants’ preferred public gym, and facilitated by a trained member of the research team. The programme involves 2–3 sessions lasting less than 1 hour each, per week, for each of the 4 weeks. Weeks 1 and 2 will be fully supervised by a member of the research team. In week 3, participants will be asked to train alone in one of the sessions, and in week 4, they will train fully independently. A 4-week programme has been selected to assess feasibility and acceptability to participants, similar to previous feasibility work carried out in our team with older people.^36^ The programme is not designed to induce changes in any physical or clinical outcomes.

The trial will be carried out once all relevant COVID-19 restrictions have been lifted in England. The research team will also adhere to COVID-19 standard operating protocols specified by the sponsor.

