### Data analysis plan

#### Quantitative analysis

This is a feasibility study to inform a larger trial and no hypothesis testing will be conducted. Consequently, quantitative data analysis will be descriptive. Mean, SD, range and 95% CI will be assessed on all quantitative data to assess response rates, numbers of individuals consented and randomised, retention rate, fidelity to the intervention, and participation in the training programme and qualitative interviews. The same descriptive methods will be used to report questionnaire and assessment data at baseline and 5 weeks. Statistical analyses will be conducted using IBM SPSS Statistics V.22 software.

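### The recruitment traffic light rests on consent uptake alone, so it can show green when few of the planned 30 participants with diabetes have been randomised

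*Protocol article*

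**What the plan says.** The Feasibility outcomes section of the protocol article sets the recruitment measure: "Recruitment rates will be calculated as the rate of invited participants who are eligible, who subsequently provide informed consent". The cut-points follow: "Green ≥50% recruitment, amber=25%–50% recruitment, red ≤25% recruitment". The colours carry a consequence: "green=proceed without modification; amber=proceed but with modification, red=unrealistic to proceed without major modification".

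The target and the calendar stand elsewhere and are not tied to the colours:

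- Study design: "Thirty participants with insulin treated diabetes and mild frailty, and thirty without diabetes will be recruited".
- Randomisation: "the diabetic group (n=30) will be randomised in a 1:1 ratio".
- Identification, recruitment and consent procedures: "The study will take place from December 2020 to September 2022".
- Intervention: "The trial will be carried out once all relevant COVID-19 restrictions have been lifted in England".

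The Quantitative analysis section lists, among the items to be summarised descriptively, "numbers of individuals consented and randomised, retention rate, fidelity to the intervention". It attaches no threshold to any of them.

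**The concern.** The third aim in the Abstract is to learn whether the diabetes group can be recruited and randomised, and recruitment is part of the primary aim under Feasibility outcomes. A trial can fall short in two ways: eligible people decline, or too few eligible people are found. The stated rule looks only at the first.

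The second is a real possibility here. The diabetes group must be aged 60 or over, on insulin, with a BMI below 30 if they have type 2 diabetes, and score 3 or 4 on the Rockwood scale, all at one centre. If such people are scarce but willing, the rule returns green. The team would then carry a recruitment approach into the next trial with a formal signal that it needs no change, although it did not deliver the sample.

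**Working it through.** **Inputs.** The definition, cut-points and meaning of the colours come from Feasibility outcomes. The planned 30 with diabetes comes from Study design and Randomisation, and the study dates from Identification, recruitment and consent procedures. The protocol gives no number of eligible invitees, so the counts below are assumptions chosen to show how the rule behaves. The article does not say whether the percentage covers the diabetes group alone or all 60; the examples take the diabetes group, the one that is randomised.

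The plan has no recruitment figure of its own to reproduce. The sample size section gives no calculation.

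**The rule as a formula.** Let *e* be the eligible people invited and *c* those who consent.

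- Uptake: *r* = *c*/*e*. The colour depends on *r* only.
- Share of target: *a* = *c*/30 = *r* × *e*/30. This is an upper limit on the share randomised, because some who consent may not reach randomisation.

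Accrual depends on both *r* and *e*; the colour does not depend on *e*.

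**Same uptake, different accrual.** Hold uptake at 60%, clear of the 50% cut-point:

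| Eligible invited | Consents | Uptake | Colour | Share of 30 |
|---|---|---|---|---|
| 10 | 6 | 60% | green | 20% |
| 20 | 12 | 60% | green | 40% |
| 50 | 30 | 60% | green | 100% |

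A further example: 8 consents from 12 is 66.7%, also green, with 8/30 = 26.7% of target.

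**General form.** *c* consents are unambiguously green whenever *e* is below 2*c*, however small *c* is. The rule contains no minimum count.

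**Does another section repair this?** Quantitative analysis reports the counts but lets none of them alter a colour. The target of 30 and the study dates enter no recruitment criterion.

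**Pace, for scale only.** December 2020 to September 2022, counting both end months, is 1 + 12 + 9 = 22 months, and 30/22 is about 1.4 per month. This is a minimum. The period is that of the whole study, including training and follow-up, and the start waits on the lifting of COVID-19 restrictions. The months open to recruitment are fewer, by an amount the article does not state.

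**The case against.** The best defence is that uptake among eligible invitees is a recognised and useful feasibility measure, and that the section speaks of the feasibility of recruitment procedures. The counts will be published, a CONSORT diagram is planned, and the Discussion ties the next step to positive data and acceptability in general terms, so a shortfall would be visible. The full protocol may also hold accrual targets.

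Most of this stands, and it limits the seriousness of the point. It does not remove it. The article states the rule, its cut-points and its consequence in full, so this is not a complaint about a missing detail. A progression rule set in advance is meant to spare the team from judging a shortfall after the event.

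The wording could also be read as eligible consenters over everyone invited. Ineligible invitees would then lower the percentage, but it would still be a ratio and would not register too few people being found to invite.

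Three stronger readings are tempting and are not supported:

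- *The colour is nearly unrelated to accrual.* Uptake is one of its two factors, so the rule is incomplete, not unrelated.
- *Red is wrong whenever 30 are recruited.* For example, 30 consents from 150 eligible invitees is 20%, which is red with the target met. But red calls for major modification, and 80% of eligible people declining is a defensible reason for that.
- *Green is more likely than not at a true uptake of 50%.* Whether that probability lies above or below one half depends on how exactly 50% is coloured, where green and amber overlap. A true rate on the cut-point says nothing about accrual in any case.

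**Conclusion.** The point holds in this limited form: the only recruitment criterion behind the traffic light is consent uptake, which cannot register a failure to find eligible people. Green is therefore compatible with any number randomised, for instance at most 6 of 30 (20%) at 60% uptake. How likely such a result is cannot be computed, because the protocol gives neither the expected number of eligible invitees nor the expected uptake.

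The conclusion rests on reading the article's rule as the operative one and on the diabetes group being the target of interest. It does not depend on the illustrative counts. The change should be made, but it is of moderate weight: no participant is affected, and the counts will be reported whatever the colour.

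**What to change.** Under Feasibility outcomes, keep the uptake percentage and its colour, and add a second recruitment criterion: the number of participants with diabetes randomised by the close of recruitment, as a percentage of the planned 30. Report it also per month actually open to recruitment, leaving out COVID-19 closure and the follow-up period after the last participant is recruited. The close of recruitment needs to be stated, since the article gives dates only for the study as a whole. The team should fix the green, amber and red cut-points for this criterion before looking at the data, and state that the overall recruitment verdict can be no better than the accrual colour.

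The cost is a sentence or two of wording. The numbers consented and randomised are already due to be summarised, so beyond recording when recruitment was open nothing new is needed, and no further participants. The downside is that the recruitment verdict may come out less favourable. Accrual affected by the pandemic will also need careful interpretation before it is projected on to a later trial.

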##### Clinical history

For all participants, information on:

Comorbid disease.Current medications, including changes in medications during the trial period.Weight loss.Exhaustion.Physical activity levels (using the International Physical Activity Questionnaire, short form).

For participants with diabetes only, information on:

Insulin regimen.Glucose monitoring (self-report).Serious hypoglycaemic episodes over the past 12 months.

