### Control arm

Participants randomised to the control arm will be asked to carry on with normal daily activities, without any changes to any exercise they might do.

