### Secondary outcomes

#### Clinical and physical outcomes

Body composition measured using height, weight, waist circumference, percentage body fat and percentage fat-free mass using bioelectrical impedance analysis at baseline and 5 weeks.Isometric strength measured using a torque and strain gauge at baseline and 5 weeks.Handgrip strength measured using a digital handgrip dynamometer at baseline and 5 weeks.Gait speed measured using three 4 m walking tests on digital timing gates at baseline and 5 weeks.Timed sit to stand, measured using five sit-to-stand movements at baseline and 5 weeks.Cardiovascular health measured using resting blood pressure, HbA1c, blood lipid profile, and inflammatory cytokines at baseline and 5 weeks.Instances of hypoglycaemia, measured weekly from baseline, obtained using patient self-report.

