### Monitoring and trial management

A data monitoring committee has not been convened given the small size and feasibility focus of this trial. The Trial Management Group will provide trial oversight and monitor any safety issues that arise.

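### Adverse events are planned for the intervention arm only, so events other than hypoglycaemia will have no concurrent control rate

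*Protocol article*

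**What the plan says.** All references are to the protocol article.

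- **Feasibility outcomes**, last sentence: "Information about adverse events will be collected for the intervention group". No other section provides for adverse event recording in controls.
- The same section, on attrition, counts people "lost to follow-up measurement for both conditions".
- **Randomisation**: "the diabetic group (n=30) will be randomised in a 1:1 ratio to either the intervention group" or the control group. **Control arm**: "Participants randomised to the control arm will be asked to carry on with normal daily activities". The comparator is therefore randomised and concurrent.
- **Clinical and physical outcomes**: "Instances of hypoglycaemia, measured weekly from baseline, obtained using patient self-report". No arm is named.
- **Clinical history**: "Serious hypoglycaemic episodes over the past 12 months" for everyone with diabetes, and "Current medications, including changes in medications during the trial period" for all participants.
- **Monitoring and trial management**: there is no data monitoring committee; "The Trial Management Group will provide trial oversight and monitor any safety issues that arise".
- **Quantitative analysis**: results are descriptive, with no hypothesis tests.

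**The concern.** The control arm comes from the same population as the intervention arm: aged 60 or over, insulin-treated and mildly frail. Its members also repeat the study tests at follow-up, including a maximal leg-extension effort and a blood draw. They can fall, strain a muscle, have a cardiovascular event or react to a test. As written, nothing commits the team to recording any of this.

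Three things are at stake:

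- A count of, say, falls or muscle injuries in the training arm has no background rate from untrained people in the same weeks.
- The group charged with safety oversight would have planned general adverse event data from one arm only.
- The Discussion foresees a further randomised trial of the same training over a longer period. A feasibility study is the place to find out whether adverse events can be collected evenly in both arms, and this one would not. Control-arm events that are not recorded at the time cannot be reliably reconstructed afterwards.

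**Working it through.** **1. Is it a rule or a gap?** The adverse event sentence names one group. Earlier in the same section, the attrition definition names both conditions. The authors specify both arms when they mean both, so the natural reading is a one-arm rule and not a detail left to another document.

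**2. What other control-arm data could stand in?**

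| Source | Covers controls? | Replaces general adverse events? |
|---|---|---|
| Weekly hypoglycaemia self-report | Yes on the natural reading; arms not named | Only for hypoglycaemia |
| Serious hypoglycaemia, past 12 months | Yes | No; hypoglycaemia only |
| Medication changes | Yes | No; at most an indirect trace |
| Loss to follow-up | Yes | No; events without dropout are missed |
| Trial Management Group oversight | No arm named | No; it needs data to review |

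Hypoglycaemia is therefore covered. Other events are not.

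**3. Size as written.** The plan states no event rate, alpha or power, so there is no figure to reproduce. Randomising 30 at 1:1 gives 30/2 = 15 per arm. All event counts below are assumptions. The exact (Clopper-Pearson) 95% limits for x events in n people are the 0.025 quantile of Beta(x, n-x+1) and the 0.975 quantile of Beta(x+1, n-x).

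- 0/15: upper limit 1 - 0.025^(1/15) = 21.8%
- 1/15: 0.2% to 32%
- 3/15 (20%): 4.3% to 48.1%
- 5/15: 12% to 62%

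These widths come from having 15 people and stay the same after the fix. What is missing is a control rate to set beside them.

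**4. What two-arm collection would give.** The Newcombe interval for a difference d = p1 - p2, with Wilson limits (l, u) in each arm, runs from d - sqrt[(p1-l1)² + (u2-p2)²] to d + sqrt[(u1-p1)² + (p2-l2)²].

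For 3/15 against 1/15, the Wilson limits are 0.071 to 0.452 and 0.012 to 0.298, and d = 0.200 - 0.067 = 0.133.

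- Lower: 0.133 - sqrt(0.129² + 0.232²) = -0.13
- Upper: 0.133 + sqrt(0.252² + 0.055²) = 0.39

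| Assumed counts | Difference (points) | 95% interval |
|---|---|---|
| 3/15 v 1/15 | 13 | -13 to 39 |
| 5/15 v 2/15 | 20 | -11 to 47 |
| 6/15 v 3/15 | 20 | -12 to 47 |

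**5. Could it test harm?** Take two-sided 0.05 and 15 per arm. The normal approximation is power = Φ[(|d| - 1.96·SE0)/SE1], with SE0 from the pooled rate and SE1 from the separate rates. The exact figure sums the binomial probabilities of all tables with Fisher p ≤ 0.05.

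| Assumed rates, control v training | Normal | Fisher exact |
|---|---|---|
| 10% v 30% | 27% | 15% |
| 20% v 40% | 22% | 11% |
| 10% v 50% | 68% | 54% |

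For the first row: SE0 = sqrt(2 × 0.2 × 0.8/15) = 0.146, SE1 = sqrt[(0.09 + 0.21)/15] = 0.141, and (0.200 - 0.286)/0.141 = -0.61, so Φ = 0.27.

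**The case against.** The strongest reply is that this is a small feasibility study. None of its traffic-light criteria uses control-arm adverse events, no between-arm comparison of them is planned, and the sentence comes directly after the acceptability and fidelity measures for the training. With 15 per arm, collecting events in both arms could not establish or exclude harm. All of that stands. It limits what the change can deliver, but it does not explain why a randomised, followed-up control group should go unrecorded when recording it is cheap.

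It can also be said that the sentence lacks the word *only*, and that an article condenses its protocol. If fuller documents provide for both arms, the article's sentence is inaccurate and still needs changing.

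A reader might infer something stronger: that the trial cannot separate training-related hypoglycaemia from the background rate, so the protocol's central safety worry goes unanswered. The documents do not support this, because weekly hypoglycaemia self-report carries no arm restriction. Nor is all safety-relevant information confined to one arm, since medication changes and loss to follow-up are recorded in both.

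A reader might also suppose that trainers see intervention participants at every session throughout. The Intervention section fully supervises weeks 1 and 2, has one session alone in week 3, and makes week 4 fully independent.

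**Conclusion.** The point holds for adverse events other than hypoglycaemia. As written, they are planned for about 15 of the 30 randomised people. The trial will have no concurrent control rate for them, will not capture harms in controls (including those from the study tests), and will not pilot two-arm collection.

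This rests on two readings: that naming the intervention group excludes controls, which the wording on attrition supports, and that the hypoglycaemia outcome applies to both arms, which is natural but not explicit. The primary feasibility outcomes are unaffected.

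It would be wrong to conclude that correcting this turns the study into a test of harm. On the assumed counts, the intervals for a difference are about 50 to 60 points wide, and exact power for 10% against 30% is 15%. The gain is a descriptive background rate and evenly ascertained events.

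**What to change.** Replace the adverse event sentence under Feasibility outcomes with wording such as: *Adverse events will be collected in both randomised arms from randomisation to the 5-week visit, with the same form and at the same times.* Use the weekly contact that the hypoglycaemia self-report already implies.

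Under Clinical and physical outcomes, state that hypoglycaemia is recorded in both arms, so that the two sections agree.

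Report events descriptively by arm: participants with at least one event, and number of events. Add no hypothesis test.

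The cost is one extra form page and about 5 short contacts for each of about 15 controls (5 × 15 = 75), largely needed already for the hypoglycaemia report. One limit remains: randomisation follows the baseline tests, so a reaction during those tests falls before this window. Reactions at the repeat tests fall within it.
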